#### Concomitant Exercise and Diet

It is possible that some subjects may be participating in some low-volume physical activity prior to study enrollment and still be eligible for the study (e.g., yoga, yard work). To control for this, all subjects will be encouraged to continue normal activity outside of the study throughout their enrollment in the study. Similarly, study subjects will be asked to maintain their normal diet throughout the study.

#### Adherence

Successful adherence will be defined as a study subject who achieves at least an 80% adherence rate (i.e., attends 29 of 36 exercise sessions).

### Data Management

Data will be entered into the database immediately after each measure is performed by the investigator collecting the measure, and then again at the end of the study by the outcomes assessor. Any incongruous measures will be re-analyzed separately by the outcomes assessor and another blinded investigator. Demographic and intervention group data will be coded and the code will be stored in a locked cabinet unavailable to the outcomes assessor.

### Statistical Methods

The three intervention arms (HIIT, MICT, and RT) will be compared against each other for all primary analyses. For total fat mass and the primary and secondary knee extensor-related outcomes (isokinetic power, muscle volume, MVC, and isokinetic fatigue), we will compute a percentage change from baseline to 12 weeks. For absolute and relative VO_2_max and 6-min walk distance we will compute absolute change from baseline to 12 weeks. We will test differences in group means using one-way ANOVA with Sidak option in SPSS v. 25.0. Tukey *post hoc* tests will be performed if significant differences exist, alpha level set at 0.05. Additionally, as this is a proof-concept, proof of mechanism trial we will calculate effect sizes between groups using the corrected effect size Hedge's g with 95% confidence intervals for small sample sizes (65).

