## Abstract

**Background:** Age-related declines in physical function lead to decreased independence and higher healthcare costs. Individuals who meet the endurance and resistance exercise recommendations can improve their physical function and overall fitness, even into their ninth decade. However, most older adults do not exercise regularly, and the majority of those who do only perform one type of exercise, and in doing so are not getting the benefits of endurance or resistance exercise. Herein we present the study protocol for a randomized clinical trial that will investigate the potential for high-intensity interval training (HIIT) to improve maximal oxygen consumption, muscular power, and muscle volume (primary outcomes), as well as body composition, 6-min walk distance, and muscular strength and endurance (secondary outcomes).

**Methods and Analysis:** This is a single-site, single-blinded, randomized clinical trial. A minimum of 24 and maximum of 30 subjects aged 60–75 that are generally healthy but insufficiently active will be randomized. After completion of baseline assessments, participants will be randomized in a 1:1:1 ratio to participate in one of three 12-week exercise programs: stationary bicycle HIIT, stationary bicycle moderate-intensity continuous training (MICT), or resistance training. Repeat assessments will be taken immediately post intervention.

**Discussion:** This study will examine the potential for stationary bicycle HIIT to result in both cardiorespiratory and muscular adaptations in older adults. The results will provide important insights into the effectiveness of interval training, and potentially support a shift from volume-driven to intensity-driven exercise strategies for older adults.

**Clinical Trial Registration:** This trial is registered with ClinicalTrials.gov (registration number: NCT03978572, date of registration June 7, 2019).

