### Sample Size

In this proof-of-concept, proof-of-mechanism trial, we report sample size estimates based on previous recommended literature (49). A sample size of ~8 subjects per group will detect a moderate effect. Sample size calculation was based on expected effect sizes for the HIIT cycle, MICT cycle, and RT groups for the primary outcomes of V0_2_max and thigh muscle CSA. Consistent with our “dual benefits hypothesis” we assumed, based on the literature, an 8% increase in thigh CSA for both the HIIT and RT groups (50) and 2% increase for the MICT group (51) and common SD across all groups of 4%. With the assumption of a 2-sided test and alpha level of significance equal to 0.05 an *n* = 7/group yields power of 0.83. With respect to VO_2_max we assumed a 32% increase in the HIIT group, a 15% increase in the MICT group, and a 10% increase in the RT group and common SD across all groups of 14% (52). With the assumption of a 2-sided test and alpha level of significance equal to 0.05 an *n* = 8/group yields power of 0.80. In line with other proof-of-concept, proof-of-mechanism trials, no statistical control for type-I error from multiple comparisons will be considered, and *p*-values will be interpreted with care, as descriptive weights of evidence rather than as confirmatory claims. Lastly, this proof of concept, proof of mechanism trial is needed to test the complex interventions proposed, and the effect sizes calculated from this trial could be used to estimate sample size for a future large-scale clinical trial. Accordingly, we plan to enroll an *n* = 8–10 subjects per group.

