## Anticipated Results

### The Dual-Benefits Hypothesis

The HIIT group will see improvements in endurance measures (VO_2_max, 6-min walk distance, isokinetic fatigue) equal to the MICT group and greater than the RT group, and improvements in muscular characteristics (isokinetic power, MVC, thigh muscle volume, VRFD, TRFD, voluntary activation) equal to the RT group and greater than the MICT group.

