The largest potential problem that could arise throughout the course of the study relates to the possibility of AEs. The risk of cardiovascular events in adults participating in HIIT programs is low, as reported by Rognmo et al. (66), who found that of the 4,800+ cardiac rehabilitation patients participating in either HIIT or MICT at a cardiac rehabilitation center, three suffered from cardiac arrest during training (one fatal during MICT, two non-fatal during HIIT). The rate of complications to the number of patient exercise hours was 1 per 23,182 h for HIIT (66). The target population for the current study will include insufficiently active older adults, but those with certain known heart conditions will be excluded from the study, and any subjects who display specific irregular cardiac responses during the baseline GXT (Table 3) will also be excluded. As such, risk of cardiac events is expected to be lower for our population than has been reported in cardiac rehabilitation patients. The American College of Sports Medicine recognizes the risks associated with exercise, but states that the health benefits of exercise outweigh the risks (15).

This study will assess the effectiveness of a high-intensity interval cycling exercise protocol in older adults to produce both cardiorespiratory and muscular adaptations. If shown to be effective it will pave the way for a paradigm shift from volume- to intensity-driven exercise recommendations for older adults, with the ultimate goal of improving health and reducing age-related physical dysfunction.

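### The stated power (0.83 and 0.80) is per outcome; under the planned ANOVA-then-Tukey analysis the two superiority comparisons that define the dual-benefits hypothesis have about 0.5 joint power at 8 per group

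*Protocol article*

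**What the plan says.** The Abstract names three primary outcomes: "maximal oxygen consumption, muscular power, and muscle volume (primary outcomes").

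The Dual-Benefits Hypothesis (under Anticipated Results) is stated as pairwise comparisons. On endurance measures HIIT is to be "equal to the MICT group and greater than the RT group, and improvements in muscular characteristics" are to match RT and exceed MICT.

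Sample Size invokes this hypothesis and bases its calculation on expected effects "for the primary outcomes of V0_2_max and thigh muscle CSA". For CSA it assumes "an 8% increase in thigh CSA for both the HIIT and RT groups", 2% for MICT and an SD of 4%, and reports power 0.83 at 7 per group. For VO2max it assumes 32% (HIIT), 15% (MICT) and 10% (RT) with an SD of 14%, and reports that "an *n* = 8/group yields power of 0.80". Both are given "With the assumption of a 2-sided test and alpha level of significance equal to 0.05". No test is named, no joint power is given, and isokinetic power has no assumption. The same section says that multiplicity will not be controlled and that p-values are descriptive.

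Statistical Methods states "The three intervention arms (HIIT, MICT, and RT) will be compared against each other for all primary analyses". It fixes one-way ANOVA with a Sidak option, Tukey tests conditional on significance at 0.05, and Hedges' g with 95% confidence intervals.

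**The concern.** The hypothesis is a conjunction: an endurance comparison and a muscular comparison must both come out in favour of HIIT. Neither 0.83 nor 0.80 is the power of that conjunction. Nor is either figure the power of the pairwise test that Statistical Methods would apply, because Tukey's critical value is higher than that of a single two-sided t-test and the test is run only after a significant ANOVA.

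Two things are at stake. A reader who sees about 0.8 next to the dual-benefits hypothesis may take it as the chance of supporting that hypothesis. And the trial gives up power on the two comparisons it most needs, through an adjustment that its own Sample Size section says it will not make. The Discussion attaches a large consequence to success: "If shown to be effective it will pave the way for a paradigm shift from volume- to intensity-driven exercise recommendations for older adults".

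**Working it through.** **Inputs (Sample Size):** CSA means for HIIT/MICT/RT 8/2/8, SD 4. VO2max means 32/15/10, SD 14. Two-sided alpha 0.05; 8 to 10 per group. **Assumed:** normal errors, no dropout, and a within-person correlation of 0 to 0.5 between the two outcomes (the protocol gives none).

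**Step 1: the plan's own figures.** Omnibus F with noncentrality λ = n·Σ(mean − grand mean)²/SD², on 2 and 3(n − 1) df.
- VO2max: grand mean 19; squared deviations 169 + 16 + 81 = 266. At n = 8, λ = 8 × 266/196 = 10.86 and power is 0.789. The stated 0.80 is reproduced closely.
- CSA: grand mean 6; squared deviations 4 + 16 + 4 = 24. At n = 7, λ = 7 × 24/16 = 10.5 and power is 0.763. The stated 0.83 is not reproduced. At n = 8, λ = 12 and power is 0.830.

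A two-sided two-sample t-test of HIIT against MICT on CSA at n = 7 gives 0.731. No single two-sided method that was tried returns both stated figures, so the test behind them is unknown.

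**Step 2: the defining pairs.** Noncentrality δ = difference/(SD·√(2/n)). At n = 8, √(2/8) = 0.5.
- HIIT − MICT on CSA: 6/(4 × 0.5) = 3.00.
- HIIT − RT on VO2max: 22/(14 × 0.5) = 3.14.

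On 21 df the two-sided 5% critical value is 2.08 for a planned contrast and 2.52 for Tukey (studentized range quantile divided by √2).

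**Step 3: single and joint power.** Tukey gated on F, and the joint figures, come from simulation with 400,000 trials per setting.

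| Method | n per group | HIIT > MICT, CSA | HIIT > RT, VO2max | Both (correlation 0 to 0.5) |
|---|---|---|---|---|
| ANOVA then Tukey | 8 | 0.68 | 0.72 | 0.49–0.52 |
| ANOVA then Tukey | 10 | 0.80 | 0.84 | 0.67–0.69 |
| Planned contrasts, pooled error | 8 | 0.82 | 0.85 | 0.69–0.71 |
| Planned contrasts, pooled error | 10 | 0.90 | 0.92 | 0.83–0.84 |

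Check at correlation 0, where the joint power is the product: 0.68 × 0.72 = 0.49; 0.816 × 0.850 = 0.69; 0.898 × 0.923 = 0.83.

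Sidak-adjusted pairs in place of Tukey give 0.46 to 0.50 jointly at n = 8. With Tukey, about 12 per group would be needed for joint power 0.80 at correlation 0.

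**Step 4: the equality parts.** The 95% interval half-width for a pairwise difference at n = 8 is t·SD·√(2/n): 2.08 × 4 × 0.5 = 4.16 points for CSA and 2.08 × 14 × 0.5 = 14.56 points for VO2max, about one SD in each case. A non-significant difference at this size therefore says little about equality.

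**The case against.** The best defence is that this is a phase 1B proof-of-concept trial. It says its p-values are descriptive and its effect sizes are meant to help size a later trial. A formal rule for combining primary outcomes is commonly left to the full protocol or analysis plan, neither of which is shown. That stands: the absence of a decision rule in this article is not in itself an error.

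Several stronger readings are tempting, and the protocol does not support them.
- A reader might infer that no comparisons are named. The Dual-Benefits Hypothesis section names them, and Statistical Methods compares all arms.
- A reader might infer that 0.83 and 0.80 are omnibus powers. Sample Size names no test, and the omnibus F does not give 0.83 at 7 per group.
- A reader might take about 0.5 as the power of the trial. It is specific to Tukey at the minimum size; 10 per group or planned contrasts raise it to about 0.7, and the two together to 0.83.
- A reader might object that the F-test cannot tell HIIT behaving like RT from HIIT behaving like MICT. That is true of the F-test alone, but the Tukey tests and effect sizes that follow do separate them.

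It can also be said that Sample Size never claims joint power, and that its statement on multiplicity may have been meant across outcomes rather than across arms. The first is correct, but the section links its inputs to a joint hypothesis without saying that the power is not joint. The second is possible, but the text does not make that distinction, and Sidak and Tukey are both multiple-comparison controls.

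**Conclusion.** The point holds in a limited form. Sizing is linked to a hypothesis made of pairwise comparisons, but power is stated per outcome and for an unnamed test, and the analysis fixed in Statistical Methods does not deliver it for those pairs. At 8 per group the planned tests have 0.68 and 0.72 singly and 0.49 to 0.52 jointly; at 10 per group, 0.67 to 0.69 jointly. At the minimum size, joint power is below 0.80 even with unadjusted planned contrasts (0.69 to 0.71). The adjusted tests and the no-control statement also need to be reconciled.

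These figures take the stated means and SDs as given and cover VO2max and CSA only. They treat the Sample Size measures, CSA and percent change in VO2max, as standing in for the analysed ones, quadriceps volume and absolute change in VO2max. They leave out isokinetic power and the equality parts, so the chance of supporting the whole hypothesis can only be lower.

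**What to change.** **Statistical Methods.**
- Test HIIT against RT on VO2max and HIIT against MICT on the muscular primary outcomes as planned contrasts with the pooled ANOVA error, at two-sided 0.05, neither gated by the omnibus F nor Tukey-adjusted.
- State that the superiority part of the hypothesis is supported only if both an endurance and a muscular contrast succeed. When both named contrasts must succeed, no alpha adjustment is needed, which fits the Sample Size statement on multiplicity.
- Label the remaining comparisons supportive.
- State in advance whether muscle volume alone, or volume and isokinetic power together, decides the muscular part. That choice is the sponsor's.
- State that equality will not be claimed from a non-significant difference.

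**Sample Size.** Name the test, say that the stated powers are per outcome, and correct or explain 0.83 at 7 per group. Add the joint power on the stated inputs, for VO2max and CSA only: about 0.70 at 8 per group and 0.83 at 10 with planned contrasts, or about 0.5 and 0.67 if Tukey is kept.

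**Cost.** Wording in two sections and no new data. The price is a less favourable stated power at the minimum sample size.

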##### Maximal oxygen uptake (VO_2_max)

VO_2_max will be obtained with a ParvoMedics TrueOne 2400 metabolic measuring system with a Hans Rudolf 3813 (Shawnee Mission, KS, USA) pneumotachometer to measure ventilation. The TrueOne 2400 is a mixing chamber system that uses a paramagnetic oxygen analyzer (range 0–25%) and an infrared, single beam, single wavelength carbon dioxide analyzer (range 0–10%). Prior to each test the system will be allowed to heat up for 30 min, and then will be calibrated according to the manufacturer's recommendations. This consists of a room air auto-calibration and a gas calibration with a single gas tank (16.00% O_2_, 4.008% CO_2_). Additionally, the flow meter will be calibrated with a 3.000-liter Hans Rudolf 5530 series syringe, with a 5-stroke calibration using different flow rates for each stroke. Ten ECG electrodes will be placed on the subject's body according to Mason-Likar procedures (54, 55). Prior to placement, the areas will be shaved with a disposable razor, wiped with an alcohol pad, and then lightly abraded with fine-grit sandpaper. The subject will be fitted with a Hans Rudolf Oro-Nasal reusable facemask (Shawnee Mission, KS, USA) with a 2-way non-rebreathing valve connected to the metabolic cart with large-bore, low-resistance tubing. The testing protocol will be explained to the subject, as well as how to communicate with investigators while wearing the facemask (i.e., hand signals). Resting VO_2_ values will be collected from the subject after 3 min of rest in a seated position on the cycle ergometer. Resting blood pressure will be taken immediately after resting VO_2_ is obtained. The subject will begin cycling on a magnetically braked cycle Lode Corival CPET ergometer (Lode B.V., Groningen, NL) at 60–80 RPMs (depending on subject comfort level) with a starting power output of 15 watts (W) for 1 min, collecting VO_2_ values every 20 s. Power output will be increased by 15 W every minute until subject can no longer continue the test or criteria have been met (Table 3). With 20 s remaining in each stage, the subject will indicate their RPE on a 6–20 Borg scale (56). With 10 s left in each stage, heart rate will be recorded from ECG readouts. Blood pressure will be taken at the beginning of even numbered stages. Subjects will be verbally encouraged throughout the test, and airflow will be provided through the use of a rotating fan. After test termination, the subject will perform a 5-min cycling cool down at 30 W. Blood pressure will be taken every 5 min for 20 min after the completion of the graded exercise test (GXT). Maximal heart rate will be determined from ECG readings during the final stage of the GXT for all subjects. Absolute VO_2_max measured in L/min will be recorded at baseline and post-intervention, and change from baseline will be used for analysis. Additionally, VO_2_max relative to body mass measured in mL/kg/min will be recorded at baseline and post-intervention, and change from baseline will be used for analysis.

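### VO2max is powered on percent change but analysed as absolute change, so the stated 0.80 is not the power of the planned test

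*Protocol article*

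**What the plan says.** - **Planning (Sample Size).** VO2max is planned on percent gains: "a 32% increase in the HIIT group, a 15% increase in the MICT group, and a 10% increase in the RT group", with "common SD across all groups of 14"%. The result at n = 8 is that this "group yields power of 0.80". Thigh cross-sectional area is also planned in percent ("an 8% increase in thigh CSA for both the HIIT and RT groups", 2% for MICT, SD 4%).
- **Outcome definition (Maximal oxygen uptake).** VO2max "measured in L/min will be recorded at baseline and post-intervention, and change from baseline will be used for analysis". The same is then said for mL/kg/min.
- **Analysis (Statistical Methods).** Absolute and relative VO2max are grouped with walk distance, for which "6-min walk distance we will compute absolute change from baseline to 12 weeks". Fat mass and the primary and secondary knee extensor outcomes, which include isokinetic power and muscle volume, use percent change instead. All are compared by one-way ANOVA, with Tukey tests to follow and Hedges' g with confidence intervals. No covariate is named.
- **Allocation (Randomization).** Blocks of three; no stratification factor is named.

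**The concern.** A power figure belongs to one variable and one test. Here the variable in the calculation is not the variable in the analysis, and it is a primary outcome. Whether the difference matters depends on how gains relate to baseline fitness. If people gain in proportion to where they start, a change in L/min or mL/kg/min carries the between-person spread of baseline as well as the spread of training response. That spread could be material in men and women aged 60–75 with BMI 18–40. The relative SD then exceeds 14%, and at the minimum of 8 per arm there is no slack.

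A second, lesser matter is that the baseline is measured but enters only by subtraction or division. With arms this small, chance gaps at baseline are likely, and neither operation fully removes the regression to the mean that follows from them.

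**Working it through.** **Inputs.** From Sample Size: means 32, 15, 10; SD 14; n = 8 per arm; two-sided alpha 0.05. Not in the article, so assumed: baseline CV of VO2max, 20–30%.

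**1. Reproduce the stated power.** One-way ANOVA, noncentral F with λ = n·Σ(mᵢ − m̄)²/SD².
- m̄ = 19; Σ = 13² + 4² + 9² = 266.
- λ = 8 × 266/196 = 10.86, with 2 and 21 df. Power = **0.789**, in line with 0.80.

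The stated figure is therefore the omnibus test on percent change.

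**2. Planned test, gains proportional to baseline.** Let percent change have mean m and SD 14, independent of baseline. Absolute change, in percent of mean baseline, then has variance 196(1 + CV²) + CV²m². The arm means stay at 32, 15 and 10.

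| CV | Variance HIIT / MICT / RT | Mean variance | λ = 2128/mean | Power (formula) | Power (simulated) |
|---|---|---|---|---|---|
| 20% | 244.8 / 212.8 / 207.8 | 221.8 | 9.59 | 0.73 | 0.73–0.74 |
| 25% | 272.3 / 222.3 / 214.5 | 236.4 | 9.00 | 0.71 | 0.71 |
| 30% | 305.8 / 233.9 / 222.6 | 254.1 | 8.37 | 0.67 | 0.68 |

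The formula averages unequal variances, so it is approximate; the simulation (40,000 trials per setting, lognormal baseline) confirms it. At 10 per arm the simulated figures are 0.84, 0.82 and 0.79, against 0.89 on percent change.

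**3. Planned test, gains additive.** If the gain and its SD are fixed amounts (32, 15, 10 and 14% of the mean baseline), baseline spread does not enter. λ is again 10.86 and power is 0.79.

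**4. Baseline as a covariate.**
- Baseline gap between two arms of 8: SE = √(2/8) = 0.5 SD. A given pair differs by more than this with probability 0.32. At 10 per arm the SE is 0.45 SD.
- Pre-post correlation implied by SD 14 with equal variances: r = 1 − 196/(2·CV²), which is 0.76, 0.84 and 0.89 at CV 20, 25 and 30.
- A gap of one SE moves the change-score contrast by (1 − r) × CV × 0.5, which is 2.5, 2.0 and 1.6 percentage points, against planned contrasts of 17 (32 − 15) and 22 (32 − 10).
- Variance of ANCOVA relative to change score: (1 + r)/2 × (1 + 1/19), which is 0.92, 0.97 and 1.00.
- Power in the additive case: 0.82, 0.80 and 0.79 with the covariate, against 0.79 without. In the proportional case, log-scale ANCOVA gives about 0.75: above absolute change at CV 20–30% (0.73 to 0.68), below percent-change ANOVA (0.79).

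**The case against.** The strongest reply is that no loss of power can be shown. The article gives no baseline mean or SD for VO2max, and with additive gains the planned test keeps its 0.79. That stands, and it limits the conclusion to a mismatch with a possible cost.

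Nor is percent change safe by default. In simulations with additive gains, ANOVA on percent change falls to roughly 0.55–0.73 at CV 20–30%, depending on how the change relates to baseline. The scale should be chosen on a stated view of how gains behave.

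A reader might also infer that all the primary outcomes are compared on raw change. They are not: isokinetic power and muscle volume are analysed as percent change, and the thigh area planning figures are in percent too. Among the primaries the mismatch is confined to VO2max.

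A reader might further infer that leaving out the covariate biases the comparison. Under randomisation, ANOVA on change is valid and unbiased on average. What remains is a conditional shift of about 2 percentage points for a one-SE gap. A large precision gain should not be claimed either: a variance ratio near 0.79 needs a pre-post correlation of 0.5, below the 0.76–0.89 that the plan's SD implies at these CVs.

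Finally, p-values are declared descriptive and up to 10 per arm may be enrolled. Both lower the stakes. They do not reconcile the sections, and the protocol says that the effect sizes found here could be used to size a later trial, so the scale carries forward.

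**Conclusion.** The mismatch holds, for VO2max only. The 0.80 was derived for percent change, and the plan tests absolute change. The consequence ranges from none (additive gains, power about 0.79) to a loss of about 5 to 11 points at 8 per arm (proportional gains, power about 0.73, 0.71 and 0.68 at an assumed baseline CV of 20%, 25% and 30%). The documents cannot say where in that range the trial lies, so it would be wrong to state that the VO2max comparison is underpowered.

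The missing baseline covariate is a secondary point. Adjustment protects against chance gaps that are likely at 8–10 per arm. Its effect on power is small, and slightly negative when the pre-post correlation is high. This is a worthwhile correction to a proof-of-concept plan, not a flaw that invalidates it.

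**What to change.** **Main change.** Put the VO2max analysis and its power on one scale, by either route:
- analyse relative change (percent change or log ratio), so that the existing percent planning figures apply; or
- keep absolute change, and restate the power for L/min and for mL/kg/min under a stated baseline SD and a stated assumption on whether gains are proportional or additive.

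Align Sample Size, the VO2max outcome paragraph and Statistical Methods accordingly.

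**Secondary change.** Include the baseline value as a covariate in the primary comparisons, on the scale chosen for each outcome. Unadjusted change can stay as a descriptive summary.

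**Cost.** A few lines of wording and one recalculation, with no new data or participants. The covariate takes one residual degree of freedom (21 to 20 at 8 per arm) and may cost a little power where the pre-post correlation is high. Muscle volume and isokinetic power need no change of scale.
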